### Outcomes {12}

The primary outcome measure is viral suppression at 12 months, determined by HIV viral copies per milliliter of blood. Viral suppression will be reported as a dichotomous variable with the threshold for viral suppression defined as < 50 copies/mL, as determined by the Abbott Alinity assay (Sensitivity Limit of Detection 20 copies/mL).

The following secondary outcome measures will be assessed at baseline, 4, 8, and 12-month timepoints:ART adherence:◦ Dried blood spots measuring levels of tenofovir-diphosphate (TFV-DP) (at 12 months)◦ Medical record abstraction of pharmacy visits and pharmacy refill data◦ Adapted Adult AIDS Clinical Trials Group self-report measure of adherence [74, 75]HIV care engagement (medical record abstraction):◦ Missed visits (# of monthly visits missed and binary indicator of any missed monthly visit)◦ Visit adherence (proportion of visits kept)◦ Gaps in care (whether > 90 days have elapsed between visits)◦ Visit constancy (# of 90-day intervals with > 1 completed visit).◦ Mental health mediators will be assessed by the following measures (all timepoints):Post-Traumatic Stress (PTSD Checklist-Civilian version for the DSM-5 (PCL-5) [76]Coping [45], adapted from [77–81].

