### Objectives {7}

The primary objective of this trial is to determine the effectiveness of ImpACT + on viral load suppression by reducing avoidant coping and traumatic stress among WLH with sexual trauma in Cape Town, South Africa.

The specific objectives are:To determine the effectiveness of ImpACT + , compared to adapted problem-solving therapy (PST), on clinical outcomes over a 12-month period among WLH with sexual trauma who are initiating ARTTo examine underlying mechanisms of change by evaluating the degree to which improvements in mental health and coping mediate intervention effects on primary (viral suppression) and secondary outcomes (adherence and care engagement)To explore the scalability of ImpACT + , guided by the Consolidated Framework for Implementation Research (CFIR) [53], to better understand facilitators and barriers to full-scale implementation

Our primary hypothesis is that a greater proportion of ImpACT + participants will be virally suppressed (primary outcome), adherent, and engaged in care (secondary outcomes) at 12 months compared to PST participants. Our secondary hypothesis is that over time, ImpACT + participants, as compared to PST participants, will report greater reductions in (1) traumatic stress and (2) avoidant coping, which, in turn, will lead to (causally mediated) improvements in ART adherence, care engagement, and viral load (VL) at 12 months.

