## Data collection and management

### Plans for assessment and collection of outcomes {18a}

Participants will go through the full trial informed consent process at baseline, after which RAs will verbally administer a battery of psychological assessments and other self-report measures in isiXhosa. Independent assessors will administer the same battery at 4-, 8-, and 12-month follow-up assessments. Assessments will take approximately 60 min and will be conducted in a private room at the clinic. Study staff will clarify any questions and refer participants who indicate high suicide risk during the interviews to the medical officers for further assessment and referral. Blood samples to measure viral load and ARV adherence via DBS will also be collected at all follow-up assessments. Relevant HIV care data will be abstracted from participants’ medical records.

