## Statistical methods

### Statistical methods for primary and secondary outcomes {20a}

To assess intervention effects on the primary outcome (viral suppression), we will compare the proportion of participants achieving HIV viral suppression at 12 month follow-up across study conditions by estimating a risk ratio and obtaining confidence intervals using robust error variances with a modified Poisson model and log link [83]. We will similarly obtain risk ratio estimates to assess intervention effects on the secondary outcomes (i.e., measures of ART adherence and care engagement) using the modified Poisson approach appropriate distribution and link function based on the outcome examined.

To examine the underlying mechanisms of the intervention effects on primary and secondary outcomes at 12 months, we will evaluate the effects of ImpACT + , compared to PST, on hypothesized mediators (e.g., levels of traumatic stress and avoidant coping). Our analytic approach will incorporate the appropriate distribution and link function depending on the distribution of these mediators. We will then examine the effect of both mediators on viral load. If the product of these two paths is greater than zero, this will serve as evidence of mediation [84]. The same approach will be utilized to evaluate the degree to which changes in traumatic stress and avoidant coping mediate intervention effects on secondary outcomes (ART adherence and care engagement).

Finally, qualitative data will be analyzed using a thematic analysis approach [85]. Memos will be written for each transcript to synthesize the emerging themes across the CFIR domains. Themes will be identified via consensus discussion after independent review of transcripts and textually coded using NVivo and/or ATLAS.ti software by multiple coders. Data display matrices will be used to examine commonalities and differences across informants [86]. A diagrammatic visual, overlaid on the CFIR framework [53] will highlight the potential barriers and facilitators to full-scale implementation.

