### Methods for additional analyses (e.g., subgroup analyses) {20b}

No additional analyses are planned.

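### Self-reported adherence (and refill data, if scored per interval) is measured four times, but the only comparison the protocol fixes is a single one at 12 months, which loses precision and does not directly answer Objective 1

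*Protocol article*

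**What the plan says.** **Schedule.** Outcomes {12} introduces the adherence and care-engagement measures with "The following secondary outcome measures will be assessed at baseline, 4, 8, and 12-month timepoints". One measure is restricted: "Dried blood spots measuring levels of tenofovir-diphosphate (TFV-DP) (at 12 months". Plans for assessment {18a} has the assessors repeat the baseline self-report battery at 4, 8 and 12 months, so self-reported adherence has one baseline and three follow-up values.

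**Question.** Objective 1 in Objectives {7} concerns effects "on clinical outcomes over a 12-month period among WLH with sexual trauma". The primary hypothesis in the same section places the adherence and engagement comparison at 12 months.

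**Analysis.** Statistical methods {20a} describes a modified Poisson comparison of viral suppression at 12 months and continues: "We will similarly obtain risk ratio estimates to assess intervention effects on the secondary outcomes". A distribution and link suited to each outcome are allowed. That sentence gives no time point. The next paragraph, on mediation, refers to "intervention effects on primary and secondary outcomes at 12 months". No visit term, repeated-measures structure or baseline covariate is named for the secondary outcomes. Covariates appear only in {20c}, in the sensitivity analyses for loss to follow-up.

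**The concern.** Where a measure is recorded afresh at each visit, a single 12-month contrast leaves three of the four recorded values out of the effect estimate. Three things follow.

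- Precision: the interval for the 12-month effect is wider than the collected data allow, because a correlated baseline value is not used.
- Question: an effect on self-reported adherence that is present at months 4 and 8 but gone by month 12 looks the same as no effect. Month 4 is the only follow-up assessment before the maintenance check-ins begin (Intervention description {11a}), so it alone reflects the weekly sessions without them.
- Partial follow-up: a woman seen at months 4 and 8 but lost by month 12 contributes no outcome to a 12-month-only contrast. The plan expects 20% loss.

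**Working it through.** **1. The plan's own figure.** Sample size {14} gives 350 women, 1:1 allocation, 80% retention, 57% versus 73%, and two-sided alpha 0.05.
- Analysed per arm: 350 × 0.80 / 2 = 140.
- Mean proportion: (0.57 + 0.73)/2 = 0.65.
- z = [0.16 × √140 − 1.96 × √(2 × 0.65 × 0.35)] / √(0.57 × 0.43 + 0.73 × 0.27) = (1.893 − 1.322)/0.665 = 0.859, so power is 80.5%.
- Required number: 139 per arm, 278 in total, and 278/0.80 = 348 against 350 stated.

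The stated 80% reproduces. It concerns viral suppression and is untouched by this point. No power is stated for the secondary outcomes.

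**2. Assumptions for a secondary measure.** None of these is in the documents: a continuous score, a standardised arm difference of 0.30, and equal correlation ρ between all visits, taken from 0.1 to 0.7. The 140 per arm is carried over from step 1.

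**3. Single 12-month contrast, no baseline.**
- SE = √(2/140) = 0.1195.
- z = 0.30/0.1195 = 2.51; power = Φ(2.51 − 1.96) = 71%.
- Detectable difference at 80% power: (1.960 + 0.842) × 0.1195 = 0.335 SD.

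**4. Same 12-month estimand, adjusted for baseline.** Variance factor 1 − ρ².

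| ρ | Factor | SE ratio | Detectable difference (SD) |
|---|---|---|---|
| 0.1 | 0.99 | 0.995 | 0.333 |
| 0.3 | 0.91 | 0.954 | 0.319 |
| 0.5 | 0.75 | 0.866 | 0.290 |
| 0.7 | 0.51 | 0.714 | 0.239 |

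Power at ρ = 0.3: z = 2.51/0.954 = 2.63, so Φ(0.67) = 75%. At ρ = 0.5: z = 2.51/0.866 = 2.90, so Φ(0.94) = 83%.

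**5. Different estimand: mean of months 4, 8 and 12, adjusted for baseline.** Variance factor (1 + 2ρ)/3 − ρ².
- ρ = 0.3: 0.533 − 0.09 = 0.443. ρ = 0.5: 0.667 − 0.25 = 0.417.
- Detectable differences for ρ = 0.1, 0.3, 0.5 and 0.7: 0.209, 0.223, 0.216 and 0.186 SD.
- If the effect is 0.30 SD at every visit, power at ρ = 0.5 is Φ(3.89 − 1.96) = 97%.
- That figure depends on the constant effect. With 0.30 SD at month 12 only, the average is 0.30/3 = 0.10; z = 0.10/(0.1195 × 0.645) = 1.30 and power falls to about 25%. With 0.30 SD at months 4 and 8 and none at 12, the average is 0.60/3 = 0.20; z = 2.59 and power is about 74%, where the 12-month contrast has nothing to detect.

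**6. Which measures this covers.**
- Self-reported adherence: repeated at each assessment, so covered.
- Pharmacy refill data: covered if scored per interval; not if accumulated to 12 months.
- Care engagement, for example "Missed visits (# of monthly visits missed and binary indicator of any missed monthly visit": counts, proportions and gaps that summarise a period. Accumulated to month 12, they already span the period in Objective 1.
- Tenofovir-diphosphate: listed as a 12-month outcome, with no baseline sample mentioned. {18a} does say "Blood samples to measure viral load and ARV adherence via DBS will also be collected at all follow-up assessments", but that does not add earlier time points to the listed outcome.

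**The case against.** The strongest reply is that much of this is silence. The secondary-outcome sentence in {20a} fixes no time point and excludes neither baseline covariates nor earlier visits, and a condensed article may leave both to the analysis plan. That stands in part: a reader might infer that baseline adjustment has been ruled out, and the documents do not say so. But every time point attached to the secondary comparison is month 12, and the model is said to follow the primary one. The text therefore describes an approach that does not match the schedule or Objective 1.

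Other stronger readings also fail:
- That all adherence and engagement results are 12-month snapshots. The engagement measures are period summaries, so an early benefit would be counted in them.
- That "No additional analyses are planned" forbids a longitudinal model. That sentence belongs to item {20b}, on additional analyses such as subgroups, and does not govern modelling under {20a}.
- That 97% is the power forgone for the planned question. It belongs to another estimand and needs a similar effect at each visit, which is uncertain when the check-ins start only after month 4.
- That the result would be biased. A 12-month comparison is a valid estimand, and it is the one the hypothesis names.

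Baseline also falls 2 weeks to 4 months after ART start. Record-based baseline values then rest on a short, variable window, and their correlation with later values may be low.

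**Conclusion.** The point holds for self-reported adherence, and for refill data if scored per interval. It is a loss of information and a mismatch with Objective 1. It is not an error that biases the result, and it does not touch the primary outcome.

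For the like-for-like 12-month contrast the gain is small to moderate: power rises from 71% to about 75% at ρ = 0.3 and 83% at ρ = 0.5, with almost nothing gained at ρ = 0.1. The larger variance reduction, to about 42% to 44% at ρ = 0.5 and 0.3, applies only to the time-averaged effect. All figures assume a continuous score, a 0.30 SD effect, equal correlation and 140 per arm. If adherence is dichotomised for a risk ratio, the gain depends on the correlation of the binary values instead. This is a worthwhile improvement at no data cost.

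**What to change.** In Statistical methods {20a}:
- For self-reported adherence, and refill data scored per interval, specify one repeated-measures model, for example GEE with robust errors and a link suited to the measure. Include arm, visit, arm-by-visit and the baseline value where a comparable one exists.
- Take the 12-month contrast from this model for the stated hypothesis. Report the average over months 4, 8 and 12 as a separate, named estimand for Objective 1.
- State that missed visits, visit adherence, gaps and constancy are accumulated over the full 12 months, without a baseline covariate where none is meaningful.
- Keep tenofovir-diphosphate as a 12-month comparison.
- Keep the loss-to-follow-up sensitivity analyses in {20c}.

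The cost is analysis wording only. The data are already scheduled, the primary outcome and visits do not change, and the text can be fixed while the analysts are masked ({17a}, {17b}).

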### Implementation and scalability

In addition to examining the efficacy of ImpACT + , this trial will include a mixed-method process evaluation of intervention feasibility and acceptability. We will explore the scalability of ImpACT + by assessing potential facilitators and barriers to full-scale implementation, guided by the CFIR [53]. The CFIR helps evaluate an intervention’s effectiveness in a specific context and identify strategies to optimize intervention benefits. We will draw on these CFIR domains: (1) intervention characteristics, (2) outer setting, (3) inner setting, and (4) process. After recruitment is complete, we will conduct in-depth qualitative interviews with clinic staff (*n* = 10 per clinic, 20 total: nurses, physicians, social workers, adherence counsellors, community health workers) and ImpACT + interventionists to explore intervention factors that would facilitate or impede roll-out and the sustainability of implementation. Interviews with clinic staff and managers at the City of Cape Town Health Department (*n* = 10) will explore patient needs and resources, and external policies and incentives that could impact future implementation and scalability. A random subset of ImpACT + participants (10%; *n* = 18) will be asked to participate in an in-depth interview on acceptability of the intervention and barriers and facilitators to implementation.

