## Methods: participants, interventions, and outcomes

### Study setting {9}

The study will be conducted in four primary healthcare facilities located in the peri-urban suburb of Khayelitsha, situated on the outskirts of Cape Town, South Africa. Khayelitsha is one of the fastest growing informal areas of South Africa, with a conservatively estimated population of 500,000 [55]. Khayelitsha is the region with the highest HIV prevalence in the Western Cape [56] and is characterized by high rates of unemployment and poverty, with almost half of residents living in overcrowded, poor quality housing without electricity, indoor sewage, and/or running water [57]. The healthcare facilities offer comprehensive HIV care, and staff are comprised of nurses, adherence counselors, community care workers, pharmacists, medical officers, and social workers. Each of the four facilities serves between 7500 and 10,000 patients living with HIV, of which two-thirds are female and a majority are Black African and isiXhosa-speaking. Universal test and treat guidelines were introduced in South Africa in 2016, and ART initiation at the clinic follows the standard protocol per government guidelines [58]. The ART initiation clinics serve naive initiators (often newly diagnosed), restarters (absent from care ≤ 3 months), and defaulters (absent from care > 3 months).

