### Eligibility criteria {10}

The study will enroll women living with HIV engaging with care at one of the four study clinics. Women will be eligible for enrollment in the trial if they meet the following criteria: (1) Living with HIV and between 2 weeks and 4 months since initiation of first-line ART (as new initiators, restarters or defaulters); (2) history of sexual abuse or assault during childhood, adolescence, or adulthood, using four items based on the WHO CIDI [59] and the Childhood Trauma Questionnaire [60]; (3) endorsement of any PTSD symptoms as assessed by the Breslau PTSD screener [61]; (4) 18 years or older; (5) isiXhosa speaking; and (6) receiving HIV care services at a study clinic. Patients will be excluded and referred to psychiatric services if they meet criteria for high risk of suicide. Suicidal ideation and severity will be assessed using items adapted from the suicidality subscale of the Mini International Neuropsychiatric Interview [62]. Pregnant women will be eligible to enroll. Additional exclusion criteria include patients initiated on second- or third-line ART, the inability to provide informed consent, or inability to communicate in isiXhosa or English.

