## Oversight and monitoring

### Composition of the coordinating center and trial steering committee {5d}

A formal coordinating center is not needed for this single-site study.

Daily support for the trial is provided by:

Principal Investigators: provides scientific oversite and responsibility.

Clinical supervisor: supervises nonspecialists interventionists.

Clinical psychologist: emotionally supports field staff.

Project director: oversees daily trial activity and supervises control.

Senior research assistant: supervises research assistants and field data collection.

Project coordinator: organizes data collection, ensures data quality, trial registration, and annual reports.

Research assistants: take informed consent, administer assessments, and schedule appointments.

The study team meets weekly.

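### The clinic-staff interview sample (10 per clinic, 20 in total) fits two clinics, but the protocol states four, so the three figures cannot all be right

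*Protocol article*

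**What the plan says.** The section on implementation and scalability plans in-depth qualitative interviews once recruitment has ended. The clinic-staff sample is given as "10 per clinic, 20 total: nurses, physicians, social workers", with adherence counsellors and community health workers completing a list of five cadres. ImpACT+ interventionists are to be interviewed as well, with no number given.

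Two further groups have their own sample sizes in the same section:

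- "Interviews with clinic staff and managers at the City of Cape Town Health Department", with n = 10.
- "A random subset of ImpACT + participants (10" per cent), with n = 18.

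The number of clinics is stated elsewhere and consistently. Study setting {9} says "The study will be conducted in four primary healthcare facilities located in the peri-urban suburb of Khayelitsha", and later "Each of the four facilities serves between 7500 and 10,000 patients living with HIV". Eligibility criteria {10} refers to "women living with HIV engaging with care at one of the four study clinics".

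The scalability question is the third specific objective under Objectives {7}. The implementation section names the inner setting as one of the four framework domains to be used.

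**The concern.** A per-clinic number and a total are two statements of the same sample, linked by the number of clinics. Here the link gives two clinics where the rest of the article has four. The article does not say that staff interviews are restricted to a subset of clinics, does not name such a subset and gives no rule for choosing one.

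What is at stake is staff coverage of the clinics. The inner-setting domain concerns the facility where the intervention would be delivered, and clinic staff are a main source on it. A team that works to a total of 20 while interviewing 10 per clinic would stop after two clinics. The other two would have no staff interviews, and the choice of clinics would be unplanned. A team that works to 10 per clinic at every clinic would need twice the interviews the total allows for.

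**Working it through.** **Inputs, all from the protocol article**

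- Staff interviews per clinic: 10 (Implementation and scalability).
- Staff interviews in total: 20 (same sentence).
- Number of clinics: 4 (Study setting {9}, stated twice; Eligibility criteria {10}).
- Listed staff cadres: 5 (Implementation and scalability).

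**Formula.** Total = interviews per clinic × number of clinics.

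**Reproducing the stated total.** The stated 20 is obtained only with two clinics: 10 × 2 = 20. With the stated four clinics, 10 × 4 = 40, so the total is not reproduced and is half the product.

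**Holding two of the three figures fixed and solving for the third**

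| Held fixed | Implied third figure | Stated | Consequence |
|---|---|---|---|
| 10 per clinic, 4 clinics | total 10 × 4 = 40 | 20 | no clinic is lost; the total is wrong |
| total 20, 4 clinics | 20 / 4 = 5 per clinic | 10 | all clinics covered; the per-clinic number is wrong |
| 10 per clinic, total 20 | 20 / 10 = 2 clinics | 4 | two of four clinics have no staff interviews |

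**Depth per cadre.** At 5 per clinic, 5 / 5 = 1 person per listed cadre per clinic on average. At 10 per clinic, 10 / 5 = 2.

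**Can another group explain the gap?** The health department interviews are listed separately with n = 10. Adding them gives 20 + 10 = 30, which is still not 40. The participant subset is a separate group and agrees with its own description: equal allocation of 350 gives 175 per arm, and 10% of 175 = 17.5, about 18. Only the staff figure fails.

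**Reach of the error.** The main sample size does not depend on these numbers. For 57% against 73%, two-sided alpha 0.05 and 80% power, the requirement is 139 per arm, or 278 in total. Allowing for 80% retention, 278 / 0.80 = 347.5, rounded up to 348, which agrees with the stated 350.

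**The case against.** The case for leaving this alone has four parts.

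1. **The total may simply be a slip.** If 10 per clinic is the intended figure, 40 interviews would be held and no clinic would be missed. This stands. The documents do not show which figure is wrong, so any loss is conditional.

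2. **The scalability aim does not rest on clinic staff alone.** A reader might infer that the conclusion on scalability would be drawn from half the settings, or that differences between clinics could no longer be described. The documents do not support either reading. Interventionists, health department informants and trial participants also contribute. The statistical methods section plans a thematic analysis that looks for commonalities and differences across informants and plans no comparison between clinics. This part of the objection stands in full.

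3. **Two clinics may have been chosen on purpose.** This is possible, and so is a figure left over from a two-clinic plan. The article says neither. A deliberate choice of two clinics would still need to be stated, with the clinics and the way they were selected.

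4. **The article's loose use of the word site adds nothing.** The oversight section says "A formal coordinating center is not needed for this single-site study", and a reader might take this as further evidence that the number of clinics is unsettled. It is not. All four facilities lie in one suburb and are served by one study team, so the phrase can mean one locality. It changes no sample size, and a single site would fit neither two clinics nor four. The section on sequence generation stratifies by clinic but gives no number, so it does not help to decide the matter.

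None of these parts reconciles 10 per clinic, 20 in total and four clinics.

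**Conclusion.** The inconsistency is certain and rests only on the article's own figures: the stated total is half of what 10 interviews at each of four clinics would give. The sentence is intact running text. Both figures appear in the article itself, so this is not detail left to a fuller document.

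The consequence is conditional. Two of the four clinics go without staff interviews only if the total of 20 is followed at 10 per clinic. If 10 per clinic binds across four clinics, the total should be 40 and nothing is lost. If 20 binds across four clinics, every clinic is covered at half the stated number per clinic.

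The reach is limited to the staff-interview component of the third objective. The primary outcome, the power calculation and the randomisation are untouched. It is a minor point, but worth correcting because the interviews are planned for after recruitment closes, so on the article's own timetable the number can be settled before that component begins.

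**What to change.** Reconcile the implementation and scalability section with Study setting {9} and Eligibility criteria {10}. The authors know which figure was meant; the options are:

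- **Keep the stated workload and cover every clinic:** state 5 per clinic across the four clinics, 20 in total. This is a change of wording only. The downside is thin coverage within clinics, with one person per listed cadre per clinic on average.
- **Keep 10 per clinic:** correct the total to 40. This doubles the staff interviews, transcripts and coding relative to the stated total.
- **Keep both 10 per clinic and 20 in total:** say that staff interviews take place in two clinics, name them and state how they are chosen. This costs one sentence, but two clinics then have no staff interviews by design, and the report should say so.

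If the aim is to hear from staff at every clinic without adding work, the first option does so. No change is needed to the trial sample size, the randomisation or the quantitative analysis.
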